## Methods

### Approach

Our project hypothesis is that TEC4Home will be a cost-effective strategy to decrease 90-day emergency department revisits and hospital admission rates and improve comfort and quality of life for seniors with heart failure.

Our evaluation includes three studies: (1) a feasibility study to introduce TEC4Home to health professionals and patients and to refine implementation and evaluation procedures, (2) a cluster RCT across British Columbia to evaluate the impact of TEC4Home with heart failure patients discharged from the emergency department and in particular the effect of this technology on rates of emergency department revisits and hospital admissions, and (3) an innovation study to run concurrently with the cluster RCT at an additional emergency department site to establish a pathway for rapid and rigorous introduction of innovation into the health system.

A cluster approach will be used to engage and allocate emergency department sites, replicating the introduction and integration of this intervention as a program and facilitating scalability to other locations. In this way, health professionals may participate in collective quality improvement, thereby ensuring that findings can be understood in context.

### Study 1: Feasibility Study (Months 7-12)

#### Purpose

The purpose of this initial feasibility study will be to assess implementation and research procedures, identify areas of quality improvement, and inform any refinement of the RCT design. The 6-month study will implement and evaluate the clinical care path for heart failure patients being discharged from the emergency department or hospital at Vancouver General Hospital (VGH) and St. Paul’s Hospital (SPH), two urban hospitals in the Vancouver region. Drawing upon the Institute for Healthcare Improvement’s quality improvement model [19], this phase will allow us to gather patient and health professional feedback about the process in terms of patient journey and clinical workflow.

#### Participants and Recruitment

We will recruit patients over a 6-month period from VGH and SPH emergency departments. All patients presenting with heart failure to emergency departments will be approached and screened for study inclusion. To be eligible for participation, patients must be aged 65 years or older with a firm diagnosis of heart failure (ie, one of the following: clinical diagnosis, chest x-ray shows interstitial or pulmonary edema, echocardiogram shows reduced ejection fraction or diastolic dysfunction). Patients need to be deemed stable for discharge from the emergency department by treating emergency physicians and will be required to sign informed consent and be willing to actively participate, have the physical and cognitive ability to perform vital sign measurements as scheduled, have the ability and agreement to engage in self-management, and have no English language or technology barriers. They must also have a family physician that consents to participating. Patients who require hospital admission for long-term observation or do not have a family physician will be excluded. Note that these criteria will be the same across all three studies. Given the numbers of heart failure patients presenting in the emergency department in this setting and the eligibility criteria, we expect approximately 150 patients would be eligible to enroll. A minimum 60% consent rate yielding a sample size of 90 patients across both hospitals is estimated with a maximum attrition rate of 15%. Study 1 is designed as a feasibility study to test and improve procedures, with a purposive sample gleaned from the feasibility study sites; thus a power calculation has not been included. Information gathered during this phase (ie, consent and attrition rates) will inform and refine the design of the cluster RCT.

Patients’ own family physicians will be invited to participate and feedback will be collected from all involved (patients and health care professionals) to improve the approach. Emergency department personnel (physicians and nurses) will be engaged to participate in implementing TEC4Home as part of regular practice and will be invited to participate in the research as a quality improvement effort.

#### Process and Outcome Measurement

Our primary and secondary outcomes are aligned with the Triple Aim framework (ie, experience of care, population health, and cost/utilization). The primary outcome will be whether or not a patient returns to an emergency department, is hospitalized, or dies within 90 days following discharge. Secondary outcomes are reduction in cost as compared to usual care, improvement of communication during transition of care, quality of life (QoL), patient experience of care, and reductions in mortality and morbidity. Working with the Patient-Centered Performance Measurement and Improvement team in British Columbia, QoL and Patient-Reported Experience Measures (PREM) will be refined during Study 1.

Additionally, patient and health professional experience and satisfaction will be collected via interviews to gather quality improvement information. For health professionals, this will include gathering perspectives on the perceived impact of the home telemonitoring.

#### Procedures and Data Collection

Eligible patients will be invited to consent once stabilized in the emergency department. Measures and tools will be administered in order for patients to assess the research process and to inform Study 2. A prestudy survey will be administered to patients that includes social demographics, health related QoL as measured by a Patient-Reported Outcome Measure (PROM) (ie, Short Form Health Survey, SF-8) [20], patient activation (ie, Patient Activation Measure, PAM-13) [21], self-care and management (ie, European Heart Failure Self-Care Behavior Scale, EHFScBS-9) [22], health care utilization, and patient attitudes towards technology. Health care utilization and patient attitudes towards technology will be assessed by instruments developed and/or adapted by the study team. Patients will receive training and be equipped with the TEC4Home system prior to discharge from the emergency department. Patients will be monitored at home for 60 days with technical support and data will be collected from biosensors and patient self-reported health status twice daily. Thirty days after the 60-day monitoring period (ie, 90 days later), each patient will be administered a poststudy survey including the QoL, patient activation, self-care and management, health care utilization, and attitudes towards technology components of the prestudy survey in addition to items related to end-user experience including satisfaction with the TEC4Home experience and usability, perceived value, willingness to pay for this type of service/equipment based on an estimated cost provided to them in the survey, and relative value of components of the service. End-user experiences will be assessed using the System Usability Scale [23], while patient satisfaction and experiences will be assessed using survey tools developed by the research team. Patients across both sites will be invited to take part in individual interviews to help investigators firmly understand their experiences using TEC4Home and to provide in-depth information to illustrate, explain, and account for outcomes.

Emergency department personnel will receive training prior to TEC4Home roll out (ie, monitoring protocol and communication strategy). At the end of the 6-month study period, all participating health professionals will be asked to take part in an end-of-study survey and interview to provide feedback on satisfaction, usability, experiences with the monitoring protocol and communication strategy, and TEC4Home’s impact on transitions for patients. Participating patients’ family physicians will be contacted and invited to participate and will be asked to provide information on how the TEC4Home feasibility study and communication strategy worked from their perspective. They will complete the same poststudy survey as emergency department personnel and will indicate their permission to be contacted for a follow-up interview similar in focus to that conducted with emergency department personnel. Monitoring clinicians will provide feedback via structured telephone interviews on usability, the monitoring protocol, and communication strategy with a focus on quality improvement to refine and inform the design of the trial to follow (Study 2). After preliminary review of the interview data for key themes relating to quality improvement of the model, focus groups will be conducted at each hospital site, with a mix of emergency department personnel, family physicians, and patients, specific to the communication strategy and issues of transition with the goal of gathering information to direct adjustments/quality improvements for the trial phase.

#### Analysis

Hospital data captured and analyzed to assess outcomes will include patient revisits and admission rates within the 90 days postdischarge from the emergency department (60 days of monitoring and 30 days of additional follow-up) and days saved. Regression analysis will be used to analyze the impacts of age, gender, ethnicity, living circumstances, and attitudes towards technology on the outcomes. Individual level administrative data for heart failure patient revisits to emergency department and admission will be reviewed. Costs per patient for equipment, set-up, connectivity, and monitoring will be calculated and included in the analysis.

Content analysis of patient and health professional interviews will be used to identify themes and resulting recommendations for quality improvement of both implementation and evaluation processes to inform Study 2.

### Study 2: Cluster Randomized Controlled Trial (Months 20-44)

#### Study Hospitals and Patients

All hospitals with an emergency department in British Columbia will be invited to participate. A total of 30 hospitals will be selected for inclusion in the study based on their similarity to other hospitals in key characteristics (see Intervention and Control Population section). All patients presenting with heart failure to emergency departments will be approached and screened for study inclusion. As noted earlier, patient inclusion/exclusion criteria are identical to those stated in Study 1.

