#### Power and Sample Size

Based on prestudy data, the expected proportion of patients experiencing the primary outcome in the control hospitals is 12% with a standard deviation across hospitals of approximately 2.4%. This SD yields an intraclass correlation coefficient of .005. Based on Ministry of Health/TELUS data from their home monitoring pilot, we expect that the intervention will reduce the proportion of patients with the primary outcome to 6%. If 30 hospitals are included in the study with an average recruitment of 30 patients per hospital (900 patients in total), the study will have a power of 84%, assuming a 2-sided alpha level of .05. We will pair-match hospitals on selected baseline variables and adjust for baseline outcome rates in the analysis to increase the power and to compensate for an intraclass correlation that may be higher than the value used in the calculation. Based on recent Vancouver Coastal Health Authority discharge data, approximately 33 heart failure patients are discharged from the emergency department per 100,000 people per year. Assuming 60% of these patients will be eligible and consent to enroll in the study, 20 patients will be enrolled per 100,000 population per year. We expect that 3 million people will be serviced by the study sites. Over an enrollment period of 18 months, we are confident that we will be able to recruit our planned sample size of 900 patients.

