#### Analysis

We will use descriptive analysis to compare baseline characteristics of emergency departments and individuals. For the primary analysis, an intent-to-treat hierarchical (mixed-effects) logistic regression model will be fit to compare the proportions of patients who experienced the primary outcome in the intervention and control arms. This model will adjust for baseline characteristics at both the emergency department (eg, prestudy emergency department revisit/hospitalization rate, service area population) and patient (eg, age, gender) level. As hospital records will supply emergency department revisit/hospital admission data, missed outcome events will be rare. Monitoring data will be analyzed using statistical process control charting techniques to allow a more comprehensive understanding of patient’s health condition over time.

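### In Study 2, patients are judged eligible and consented after their hospital is randomised, so identically worded criteria may select different patients by arm, and the safeguards described do not remove this.

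*Protocol article*

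**What the plan says.** All places are in the protocol article.

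- **Order of events.** Hospitals are matched in pairs and one of each pair is randomised to the intervention (Intervention and Control Population). The timeline (Phase 2) puts site randomisation in months 18 to 23 and lists recruitment protocols and staff training after it in the same block. Patients are invited to consent one at a time once stabilised in the emergency department (ED) (Study 1, Procedures and Data Collection). Study 2 takes over that screening procedure (Study 2, Data Collection Procedures).
- **Who is screened.** "All patients presenting with heart failure to emergency departments will be approached and screened for study inclusion" (Study Hospitals and Patients). The next lines there say that the criteria are the same as in Study 1.
- **The criteria** (Study 1, Participants and Recruitment). "Patients need to be deemed stable for discharge from the emergency department by treating emergency physicians". Patients must also be able to take the scheduled measurements, agree to self-management and have no language or technology barrier. "They must also have a family physician that consents to participating".
- **The model** (Study 2, Analysis). The primary analysis is an intent-to-treat mixed-effects logistic regression. It adjusts at ED level, with the prestudy revisit or hospitalisation rate and service area population as examples, "and patient (eg, age, gender) level". Baseline characteristics of departments and individuals are compared descriptively.
- **Power** (Power and Sample Size). With 30 hospitals, 900 patients, 12% versus 6% and an intraclass correlation of .005, "the study will have a power of 84%, assuming a 2-sided alpha level of .05". Eligibility and consent together are put at 60% of discharged heart failure patients, with no split by arm.

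**The concern.** Randomising hospitals balances hospitals. It balances patients only if those enrolled are chosen without regard to arm. Here the choice comes after allocation. Intervention patients are trained and equipped before discharge, so recruiters and patients will in practice know the arm. The article does not say this in words. It follows from the sequence, and no masked recruiter or identification of patients before allocation is described.

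Several criteria rest on judgement about use of the device. Where a tablet and sensors must be handed over, a technology barrier is put to the test at once. Under usual care nothing tests it in the same way. A family physician may respond differently to a monitoring programme than to a usual-care study. A treating physician who can offer daily monitoring may also judge stability for discharge differently. These mechanisms could leave intervention enrolees at lower or at higher risk than controls.

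Any such difference goes straight into the primary comparison. Intent-to-treat keeps patients in their hospital's arm but does not change who was enrolled. Pair matching and ED-level covariates describe the hospital, not the patients selected within it.

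**Working it through.** **Inputs from Power and Sample Size.** Control risk 12%, between-hospital SD 2.4%, intervention risk 6%, ICC .005, 30 hospitals of 30 patients (450 per arm), two-sided alpha .05. Also 33 heart failure ED discharges per 100,000 per year, 3 million people, 18 months, 60% eligible and consenting.

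**1. The plan's power.** Design effect = 1 + (30 − 1) × 0.005 = 1.145. Effective n per arm = 450 / 1.145 = 393. SE = √[(0.12 × 0.88 + 0.06 × 0.94) / 393] = 0.0203. Power = Φ(0.06 / 0.0203 − 1.96) = 84.0%, or 83.8% with a pooled null variance. The stated 84% reproduces. The article says "This SD yields an intraclass correlation coefficient of .005"; 0.024² / (0.12 × 0.88) = 0.0055, which lowers power only to 83.3%. There is no arithmetic error behind this point.

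**2. Room for selection.** 33 × 30 × 1.5 = 1,485 discharges. 60% of these is 891 enrolled, so about 594 (40%) are not enrolled.

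**3. Illustration: no true effect, lower risk in intervention enrolees.** The shift d is assumed. Control risk stays at 12%, effective n is 393 per arm and no covariate corrects the shift. With p = 0.12 − d, SE₀ the pooled and SE₁ the unpooled standard error,

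P(significant) = Φ[(d − 1.96 SE₀) / SE₁] + Φ[(−d − 1.96 SE₀) / SE₁].

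| Assumed shift | Intervention risk | Apparent odds ratio | P(significant) |
|---|---|---|---|
| 0 | 12% | 1.00 | 5% |
| 1 point | 11% | 0.91 | 7% |
| 2 points | 10% | 0.82 | 15% |
| 3 points | 9% | 0.73 | 28% |
| 4 points | 8% | 0.64 | 46% |

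For 2 points, SE₀ = SE₁ = 0.0223, so Φ(−1.06) + Φ(−2.86) = 0.144 + 0.002 = 0.146.

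**4. What could produce such a shift.** Assume 30% of control enrolees are frail, with 20% to 24% risk, the overall risk staying at 12%. If the frail share among intervention enrolees is 15%, their risk is 1.7 to 2.6 points lower, and the false-positive rate is 12% to 21%.

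**5. The other direction.** Assume 10% of intervention enrolees are extra discharges at twice the 6% risk. Then 0.9 × 6% + 0.1 × 12% = 6.6%, and power for 12% versus 6.6% is about 74%.

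**6. How informative an all-discharge check would be.** Assume 60% participate with the full effect and the rest stay at 12%: 0.6 × 6% + 0.4 × 12% = 8.4%. With 1,485 / 30 = 49.5 patients per hospital, the design effect is 1 + 48.5 × 0.005 = 1.2425 and effective n per arm is 742.5 / 1.2425 = 598. SE = √[(0.12 × 0.88 + 0.084 × 0.916) / 598] = 0.0175. Power = Φ(0.036 / 0.0175 − 1.96), about 54%. The 1,485 are not split by age. Restricting to 65 or over removes only non-participants, so both the count and the dilution would fall.

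**The case against.** The article does state safeguards. All heart failure patients are to be approached, the criteria are the same at every site, and baseline characteristics are compared. The covariate lists are examples, and the full list, sensitivity analyses and screening counts may sit in an analysis plan that is not shown. All of this stands, and it limits the point to the recruitment design that the article itself sets out. Approaching everyone does not control who is then judged eligible or who agrees, and a descriptive comparison shows imbalance only in what was measured.

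Three stronger readings are not supported:

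- A reader might infer that the model adjusts only for age and gender. It also adjusts at ED level, and both lists are open.
- A reader might infer that the device-related criteria are hardly applied at usual-care sites. The article says that they apply equally. Only the possibility of different application can be argued.
- A reader might infer a bias as large as the effect sought. That effect is 6 points. The illustrations use 4 points or less, and nothing in the article says how large the shift would be.

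The all-discharge check also has limits. It is diluted, and it removes selection by eligibility and consent but not arm differences in who is discharged.

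**Conclusion.** The point holds in a limited form. Enrolment follows allocation, eligibility includes judgements that may be made differently by arm, and the measures described do not remove patient-level selection. Its actual size is unknown. The 15% and 28% false-positive rates apply only under assumed shifts of 2 and 3 points from 12%, with no true effect and no covariate correction. Adjustment for strong predictors would reduce them. The bias could run in either direction. The plan should be changed because the means to reduce and check it are largely in place. This does not show that the trial's comparison is invalid.

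**What to change.** 1. **Primary model.** Prespecify prior ED visits and admissions and baseline SF-8 as patient-level covariates, in addition to age and gender. The Study 1 prestudy survey covers health care utilisation and SF-8, and both Study 2 arms complete it. The article does not itemise the utilisation instrument, so confirm that it records ED visits and admissions. Cost: model wording.
2. **Supportive sensitivity analysis.** Compare by allocated arm, regardless of consent, 90-day ED revisit, admission or death among all heart failure ED discharges aged 65 or over at the 30 hospitals during the trial period. Use the hospital and provincial records already named as the main outcome source. State in advance that it is a check diluted by non-participants, so a null result does not refute the primary result. Cost: one further extraction, subject to data approvals.
3. **Discharge and enrolment flow.** Because item 2 does not remove arm differences in who is judged fit for discharge, compare by arm the number and baseline risk of heart failure ED discharges. Report screened, eligible and consented counts by arm against that denominator. Cost: screening logs and a table.

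If the analysis plan already contains these items, a reference to it is enough.

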#### Intervention and Control Population

Study hospitals will be selected and matched with control hospitals in pairs based on the 90-day emergency department revisit or hospital admission rate prior to randomization, emergency department staffing (ie, ratio of certified emergency physicians to family physicians in emergency department workforce, number of individual physicians), service area population, and annual number of emergency department visits. One hospital in each pair will be randomly assigned to receive the TEC4Home intervention and the other will remain with usual care. Hospitals will be matched and randomized within each Health Authority in British Columbia, as each Authority will commence the trial at different times according to the size of the population it serves. Sites in Health Authority groupings will enroll in the 18-month study period (in descending order according to size of population served) at the beginning of each subsequent month. At the end of each Authority’s 18-month trial period, emergency departments will participate in an additional total 90 days of monitoring (60 days) and follow-up (30 days) to ensure complete data is gathered for any patients enrolled within the last month of the study period. The intent of this approach is to maximize geographic balance for both equitable opportunity and generalizability purposes. Hospitals for which no appropriate match can be identified will be excluded.

#### Power and Sample Size

Based on prestudy data, the expected proportion of patients experiencing the primary outcome in the control hospitals is 12% with a standard deviation across hospitals of approximately 2.4%. This SD yields an intraclass correlation coefficient of .005. Based on Ministry of Health/TELUS data from their home monitoring pilot, we expect that the intervention will reduce the proportion of patients with the primary outcome to 6%. If 30 hospitals are included in the study with an average recruitment of 30 patients per hospital (900 patients in total), the study will have a power of 84%, assuming a 2-sided alpha level of .05. We will pair-match hospitals on selected baseline variables and adjust for baseline outcome rates in the analysis to increase the power and to compensate for an intraclass correlation that may be higher than the value used in the calculation. Based on recent Vancouver Coastal Health Authority discharge data, approximately 33 heart failure patients are discharged from the emergency department per 100,000 people per year. Assuming 60% of these patients will be eligible and consent to enroll in the study, 20 patients will be enrolled per 100,000 population per year. We expect that 3 million people will be serviced by the study sites. Over an enrollment period of 18 months, we are confident that we will be able to recruit our planned sample size of 900 patients.

